### Adherence

Adherence to the exercise intervention will be recorded by the ATs using each participants’ treatment file.

### Co-interventions

At the end of the study, participants will be asked to report any co-interventions (e.g., chiropractic, physiotherapy, osteopathy, massage therapy) during the intervention. Pain medication will be allowed since it is unethical to deny medication, and will be recorded for all participants.

### Data integrity

The database will be saved and preserved on a secured network at the Concordia University institution. Any inconsistencies in the data will be stated, investigated and resolved. Study staff will be the only individuals with access to the password-protected database. Investigators will permit verification of the data from the ethics board, and maintain sufficient and accurate records of documents. Any changes to the protocol will be reported and communicated to the REB. Confidentiality of the data will be protected and preserved during and after the study. Data will be kept at Concordia University for a minimum of 5 years after the end of the study.

### Sample size justification

While the effect aquatic therapy on paraspinal and gluteal muscles morphology and composition has never been investigated in chronic LBP, previous studies [35, 75, 76], showed significant improvement in multifidus muscle cross-sectional area (CSA) following other exercise interventions with medium to large effect sizes. Based on these studies, we used a mean effect size of 0.73 to calculate our sample size at a level of confidence of 0.05 and 80% power. Accordingly, a sample size of 17 participants in each group will be recruited.

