However, it is difficult for those with LBP to perform strengthening exercises without avoiding the weight load on their spine [28]. In addition, fear avoidance beliefs which refer to fear of physical movement and work activities that may elicit pain is very common in individuals with chronic LBP [11, 12]. One form of exercise that has been suggested as a promising and safer treatment alternative for individuals with LBP is aquatic exercise, with less risk of injury and difficulty performing exercises [14, 29–35]. Water immersion decreases axial loading of the spine and, through the effects of buoyancy, allows the execution of movements that are usually difficult to perform on land by reducing stress in joints [36, 37]. The unique properties of water, such as buoyancy, allow a water-based exercise program to be tailored to the needs of those suffering from LBP. Aquatic exercise may improve pain and disability [38], and maintain quality of life in individuals with chronic LBP [35], especially in individuals with low levels of physical fitness [39, 40]. Improvements in muscle strength [41] and cardiovascular fitness [31, 42] through continuous limb movements against water resistance have been reported as well. A recent systematic review and meta-analysis on the effect of aquatic therapy in LBP, showed that this may not only be an effective alternative to conventional LBP treatments, but also a safe and enjoyable substitute to improve physical function [38]. These findings suggest the potential benefits of aquatic exercise for individuals with chronic LBP.

Recent reviews concluded there is no clear particular form of exercise that is more effective than others [17–19]. Interestingly, when comparing aquatic therapy to land-based exercise in individuals with chronic LBP, some study results have showed no significant differences in decreased pain levels or improved functional ability between the two exercise types [31, 34]. However, one study showed better improvements in functional ability in the aquatic therapy group compared to the land-based exercise group [35]. Moreover, Psych et al. showed that aquatic therapy produced comparable back and gluteal muscle activation and intensity to land-based exercise [43]. Overall, there are some inconsistencies between studies comparing aquatic therapy to land-based exercise in individuals with chronic LBP.

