
### Hypotheses

It is hypothesized that participants in the aquatic therapy group will show a significant improvement in 1a) paraspinal and gluteal muscle size and 1b) paraspinal and gluteal strength following the intervention, as compared to the standard care group. We also hypothesized that both groups will show improvements in pain, disability, quality of life, and psychosocial factors following the completion of the intervention, however the effects will be greater in the aquatic group as compared to the standard care group. Finally, we hypothesized that it will be feasible to implement the app in both the standard care and aquatic exercise groups, and that participants will be compliant and satisfied with the application.

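### The stated 80% power at 17 per group does not follow from the stated inputs for the planned between-group comparison: with no pre-post correlation given, 0.73 needs 31 per group, and 17 gives about 54%

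*Protocol article*

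**What the plan says.** Sample size justification in the protocol article points to earlier studies that "showed significant improvement in multifidus muscle cross-sectional area (CSA) following other exercise interventions with medium to large effect sizes". On the basis of these studies it reports: "we used a mean effect size of 0.73 to calculate our sample size at a level of confidence of 0.05 and 80% power". It concludes: "Accordingly, a sample size of 17 participants in each group will be recruited". It does not name the test, whether it is one- or two-sided, whether 0.73 is a within-group or a between-group effect, which SD standardises it, or any correlation between baseline and follow-up.

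The comparison to be powered is between arms. Hypotheses predicts better muscle size and strength in the aquatic arm "following the intervention, as compared to the standard care group". The Methods part of the Abstract plans to compare pre-post changes between the groups. Statistical analysis specifies a repeated-measures ANOVA with a between-subjects factor, and Data collection gives two measurement times, baseline and 10 weeks.

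**The concern.** The sources are described as showing improvement after exercise, which reads most naturally as change from baseline within a group. A sample size for detecting such a change in one group does not power a comparison of the changes in two groups. The two-group contrast carries the sampling error of both arms, so at the same standardised effect it needs nearly twice as many participants in each arm.

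At stake is how the main result will be read. Readers told that the trial has 80% power will take a non-significant difference between aquatic and land-based exercise as fairly strong evidence against an effect of the planned size. If the power is nearer 54%, such a result says much less.

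**Working it through.** **Inputs.** Effect 0.73, alpha 0.05, power 80% and 17 per group, all from Sample size justification; 1:1 allocation from Randomization. A two-sided test is assumed because none is stated; one-sided was also tried. Power is from the exact noncentral t distribution.

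**Step 1: reproduce the 17.** For a paired (one-group) test the noncentrality is d × √n, with n − 1 degrees of freedom.
- n = 17: 0.73 × √17 = 3.01 on 16 degrees of freedom; power 80.7%.
- n = 16: power 77.9%.
- Solving for 80% gives n = 16.75, rounded up to 17, which is the stated number.

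**Step 2: the planned comparison.** With two time points, the group-by-time test in a repeated-measures ANOVA is the two-sample t-test on change scores. Its noncentrality is d × √(n/2), with 2n − 2 degrees of freedom and d in SDs of change.
- n = 17 per group: 0.73 × √8.5 = 2.13 on 32 degrees of freedom; power 54.2%.
- Solving for 80% gives n = 30.45, so 31 per group (62 in total). As a check, the normal approximation is 2 × (1.960 + 0.842)² / 0.73² = 29.5, so 30.
- Difference detectable with 80% power at 17 per group: d = 0.99.

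**Step 3: would one-sided testing explain 17?** No. One-sided, the two-sample test needs 24 per group (power 66.9% at 17) and the paired test needs 14.

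**Step 4: suppose 0.73 is a between-group difference in raw SDs.** The answer then depends on the pre-post correlation r, which is not stated, so a range is shown. The effective d is 0.73 / √(2(1 − r)) for the change score or group-by-time test, and 0.73 / √(1 − r²) for ANCOVA (ignoring the one degree of freedom spent on the covariate).

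| Assumed r | Change score: effective d | Power at 17 per group | ANCOVA: effective d | Power at 17 per group |
|---|---|---|---|---|
| 0.5 | 0.73 | 54% | 0.84 | 66% |
| 0.7 | 0.94 | 76% | 1.02 | 82% |
| 0.9 | 1.63 | >99% | 1.67 | >99% |

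For 80% the effective d must reach 0.991, so the squared scaling factor is (0.73 / 0.991)² = 0.543. For the change score, 2(1 − r) = 0.543 gives r = 0.73. For ANCOVA, 1 − r² = 0.543 gives r = 0.68.

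**Step 5: another route to 34 in total.** A repeated-measures interaction with f = 0.25 and r = 0.5 also returns N = 34. Its noncentrality parameter is 0.25² × 34 × 2 / 0.5 = 8.5. Equating this to d² × 17/2 gives d = 1.0 SD of change. This route therefore does not use 0.73.

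**The case against.** The strongest reply is that repeated measures gain efficiency. Repeat MRI of the same muscle on the same scanner could correlate highly, and step 4 shows that 17 per group then reaches 80% or more. This stands as a possibility. It would be wrong to say that 17 can arise only from a within-group calculation, or that the trial is known to lack 80% power. But the defence needs a between-group effect in raw SDs and a correlation, and the article gives neither. The ANCOVA variant also departs from the repeated-measures ANOVA that is named.

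It is also fair to say that the within-group origin of 0.73 is inferred from wording. The cited studies are not at hand and may have reported between-group effects.

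Three further inferences are tempting but not supported:
- **Both arms are expected to improve, so the between-group effect must be below 0.73.** Hypotheses predicts improvement in both arms for pain, disability, quality of life and psychosocial factors. For muscle size it predicts only an advantage for the aquatic arm.
- **Reference 35 has distorted the 0.73.** Background describes it as a comparison of aquatic and land-based exercise on functional ability. Sample size justification cites it for multifidus area after other kinds of exercise, and says the effect of aquatic therapy on these muscles has never been studied. The two descriptions need reconciling, but a slip in the reference number would explain them and leave 0.73 untouched.
- **The absence of a dropout allowance is an error.** A condensed article may leave this to the full protocol.

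Condensation does not excuse the main point. The article presents 17 as the result of the listed inputs, and for the comparison it plans that result does not follow.

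**Conclusion.** The point holds in a limited form: the 80% is unsupported for the between-group comparison, but it is not shown to be false. On the stated inputs, with no pre-post correlation, 17 is the two-sided paired answer. The two-sample answer is 31 per group, and 17 per group gives about 54% power with a detectable difference of about 0.99 SD of change. These figures assume a two-sided alpha of 0.05, complete data, and 0.73 measured in SDs of change (or in raw SDs with r = 0.5). Under a raw-SD between-group reading, change-score power runs from 54% to above 99% as r goes from 0.5 to 0.9. The arithmetic is certain; which calculation the sponsor actually ran is not.

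**What to change.** Revise Sample size justification to:
1. Name the test and state whether it is one- or two-sided.
2. Say whether 0.73 is a within-group or a between-group effect, and whether it is in SDs of change or raw SDs.
3. Give any pre-post correlation used, with its basis.
4. Restate the power of 17 per group for the between-group comparison: about 54% at 0.73, with a detectable difference of about 0.99 SD, unless a between-group effect and a correlation that support a higher figure are justified.
5. Check reference 35 against its description in Background. Correct the citation if it is a slip, and revise 0.73 only if that source was wrongly included in the mean.

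The cost is one rewritten paragraph and a less favourable stated power. No extra patients are needed.

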**Methods:**

This study will include 34 participants with chronic non-specific LBP and moderate to severe disability, aged between 18 and 65, who will be randomly assigned (1:1) to the aquatic exercise group or land-based standard care exercise group. Both groups will receive 20 supervised sessions, twice per week over 10 weeks. MRIs will be obtained along the lumbosacral spine (L1-L5) and pelvis at the start and end of the intervention to assess the effect of each exercise intervention on paraspinal and gluteal muscle size and quality. Pre- to post-intervention changes in all outcomes between each group will be assessed, and the association between the changes in back muscle quality and clinical outcomes will be examined. Between-subjects repeated measure analysis of variance will be used to examine the changes in paraspinal muscle morphology over the different time points. Linear mixed models will be used to assess whether baseline scores can modify the response to the exercise therapy treatment.

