### Randomization

After providing written informed consent, participants will be randomly assigned to treatment groups (1:1) using consecutively numbered sealed opaque envelopes (e.g., computer-generated randomization sequence with permuted blocks) created by an individual not involved in the study.

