### Data collection

All outcomes will be obtained at baseline for both intervention groups. All baseline assessments (e.g. MRI, strength, questionnaires) will be repeated at the end of the intervention during a 10-week follow-up (refer to Table S1 in Appendix). All self-reported questionnaires will be completed in-person using paper forms. Imaging outcomes (e.g., MRI) and lumbar extensor muscle assessments (e.g., strength) will be acquired at the School of Health, Concordia University. Demographic characteristics will be acquired via a self-reported questionnaire at baseline, after randomization.

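### The calculated 17 per group is also the number recruited, with no stated allowance for loss, so on the reading that reproduces 17 the printed 80% power holds only if every participant has both MRIs

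*Protocol article*

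**What the plan says.** The sample size section of the protocol article gives three inputs. The effect size is set by the words "we used a mean effect size of 0.73 to calculate our sample size", and the error rates by "at a level of confidence of 0.05 and 80% power". The effect is drawn from earlier studies that "showed significant improvement in multifidus muscle cross-sectional area (CSA) following other exercise interventions with medium to large effect sizes". The conclusion follows directly: "Accordingly, a sample size of 17 participants in each group will be recruited". The abstract confirms the total: "This study will include 34 participants with chronic non-specific LBP".

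The primary outcome is multifidus size and composition on MRI. The Data collection section says that the baseline assessments, MRI included, "will be repeated at the end of the intervention during a 10-week follow-up", so there are two scans per participant. The Statistical analysis section tests changes in the muscle measures with a repeated measures ANOVA. The article gives no expected loss rate, inflation step or number expected to complete both scans.

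**The concern.** A power calculation returns the number of participants needed in the analysis. The article turns that number into the number recruited. With only two time points, a participant contributes a change in muscle size or composition only if the second scan is done and usable. That scan comes after 20 supervised sessions over 10 weeks, in people with moderate or severe disability. If 17 is the uninflated answer, any missing second scan leaves the analysis short of the number behind the printed 80%.

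What is at stake is how the result is read. A null finding would be set against a stated 80% that the enrolment plan may not deliver.

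**Working it through.** **Inputs.** From the sample size section: d = 0.73, alpha = 0.05, power 80%, 17 per group. From the abstract: 34 in total, 1:1. Not given, so assumed here: two-sided testing, the number lost per group, and the pre-post correlation.

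**Step 1: reproduce 17.** For a paired (one-sample) t-test with n analysed, the noncentrality is d√n on n − 1 degrees of freedom. Power is the probability that the noncentral t exceeds the two-sided 5% critical value in absolute size.

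- n = 17: 0.73 × √17 = 3.01, critical t (16 df) 2.12, power 80.7%.
- n = 16: 0.73 × √16 = 2.92, critical t (15 df) 2.13, power 77.9%.

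So 17 is the smallest n that reaches 80%, with no inflation. A two-sample t-test, with noncentrality d√(n/2) on 2n − 2 df, needs 31 per group and does not reproduce 17.

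**Step 2: remove participants.** Losses of 1, 2 and 3 out of 17 are 6%, 12% and 18%.

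| Analysed per group | Paired, two-sided | Two-group t-test, two-sided |
|---|---|---|
| 17 | 80.7% | 54.2% |
| 16 | 77.9% | 51.5% |
| 15 | 74.8% | 48.8% |
| 14 | 71.4% | 46.0% |

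From the unrounded values, two losses per group cost 5.8 points on the paired reading (80.66 − 74.84) and 5.3 on the two-group reading (54.15 − 48.83).

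**Step 3: the planned analysis.** For the group-by-time test in a repeated measures ANOVA with two groups and two time points, take f = 0.73/2 = 0.365. The noncentrality is f² × N × 2/(1 − ρ) on 1 and N − 2 df, where ρ is the pre-post correlation. This takes 0.365 as the interaction effect size, which is itself an assumption.

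| Total analysed | ρ = 0 | ρ = 0.5 |
|---|---|---|
| 34 | 83.1% | 98.5% |
| 30 | 77.9% | 97.1% |
| Cost of two losses per group | 5.2 points | 1.4 points |

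At ρ = 0 and 32 analysed (one loss per group), power is 80.7%.

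**Step 4: detectable effect.** With 15 analysed per group, the effect detectable with 80% power is 0.78 on the paired reading and 1.06 on the two-group t-test, against the 0.73 assumed.

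**The case against.** A reader might infer that attrition costs about 6 points of power whichever test was meant, and that one loss per group always takes the trial below 80%. The document supports neither. The planned analysis is a repeated measures ANOVA, and the cost of loss there depends on a correlation that the article does not give: about 5 points at 0, about 1 at 0.5. One loss per group leaves 80.7% at correlation 0. Sidedness is not stated either, and a one-sided paired test still has 85.1% with 15 analysed. On the plain two-group test, power is far below 80% before anyone is lost, so loss does not take it across that line.

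Nor is it proved that no allowance was made. A normal-approximation paired calculation gives 14.7, rounded up to 15, and 15/(1 − 0.10) = 16.7 also rounds up to 17. The text reports no such step and the exact calculation gives 17 directly, so the uninflated reading is the more likely one, but it remains an inference.

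Two further objections carry weight. The loss rates are assumed. And the larger weakness lies elsewhere: the hypotheses compare the groups, and a plain two-group comparison at d = 0.73 has 54.2% power even with complete data.

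It could also be said that a journal article may leave attrition to the full protocol. That would answer a complaint about how missing scans are to be handled. It does not settle this point, because the article itself states the inputs, the power and the recruitment number and links them directly.

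**Conclusion.** The point holds in a limited form. The article makes its calculated number the recruited number and states no allowance for loss. On the two-sided paired reading, which reproduces 17, the 80% applies only with complete second MRIs, and power falls to about 75% with two losses per group and about 71% with three. The size on any other reading depends on the test, its sidedness and the pre-post correlation, so no single cost can be quoted. The conclusion rests on d = 0.73, alpha 0.05, assumed losses, and the inference that 17 contains no hidden allowance. It is worth correcting but is secondary to the mismatch between a number that fits a within-group test and a hypothesis between groups. Allowing for attrition alone would not give the between-group comparison 80% power on a plain two-group test.

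**What to change.** Keep 34 enrolled. In the sample size section:

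- say that 17 per group is the number randomised;
- state the number expected to have both MRIs under an explicit loss assumption (15 per group, for example, corresponds to 12% loss);
- name the primary between-group test, with its sidedness and any pre-post correlation used;
- give power or the detectable effect for that test at the expected number, in place of the unqualified 80%.

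If 17 already includes an allowance, say so and give the number before inflation.

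The cost is a few sentences and no extra participants. The downside is that the stated power will probably look less favourable, markedly so if the named test is a plain two-group comparison.

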### Statistical analysis

Primary and secondary outcome measures will first be analyzed using descriptive statistics. Changes in paraspinal and gluteal muscle measurements of interest will be assessed for all time points using between-subjects repeated measure analysis of variance (ANOVA). Linear regression models will be used to evaluate the association between paraspinal muscle morphological and functional changes with variations in disability/function status, pain, pain related fear, depression, and anxiety, while accounting for potential confounding factors. Feasibility outcomes related to the use of the “play the pain” application will include adherence rate, and satisfaction will be collected through administration data and end-of-study survey. Survey questions will be answered via a combination of Likert scale, visual analogue scale and will also include questions about barriers and facilitators to the use of the application. Our threshold for adherence and satisfaction outcomes will be 70% out of 100%. Descriptive statistics will be used to summarize the feasibility outcomes.

### Dissemination of findings

The results of this trial will be published in peer-reviewed journals and presented at notable scientific conferences. After publication of manuscripts, data request can be presented to the principal investigator (MF).

## Discussion

LBP is one of the most disabling diseases and carries a large burden globally. Exercise therapy is the most widely used form of treatment for chronic LBP and is recommended as a first-line treatment for the improvement of pain, quality of life, depression and disability/functional status. Aquatic therapy is a more comfortable alternative exercise for people with chronic LBP, with promising results in pain and function. If specific targeted lumbar muscle exercises are to be prescribed and used clinically, the evaluation of physiological muscle changes, such as hypertrophy and reversal of fatty infiltration and whether they mediate improvements in functional status should be considered when assessing the effectiveness of different exercise interventions, such as aquatic therapy and land-based exercise. This study aims to explore the potential benefits of structured water-based exercises that target trunk stabilization and hip muscles on paraspinal and gluteal muscles versus a land-based standard care exercise program. Our research protocol through measurement of muscle morphology and function, clinical symptoms and psychological factors will shed some light into this field.

The results of this trial could have significant implications for clinical practice, enhancing the management and treatment of LBP through the implementation of targeted, cost-effective interventions and clarify whether the use of a digital application in a clinical setting is feasible and can enhance the communication between patients and therapists. This study will generate valuable scientific evidence to support the implementation of a comprehensive LBP program. Such a program could help treat and train individuals with LBP to regain their physical function, mental health, and overall quality of life. Overall, the results of this trial are expected to improve the efficacy of prescriptive exercise training in participants with non-specific chronic LBP.

The limitations of this study include restricting inclusion to those able to understand and read English or French, which will decrease the generalizability of this study. Furthermore, true blinding of exercise supervisors/providers is not possible within an exercise trial.

